#### **iv. *Consent and early mortality***

The early mortality rate following acute stroke is approximately 10%. These patients are usually identified on admission and treated palliatively. However, unexpected deaths also occur. Exclusion of patients that die soon after admission would reduce the study's relevance for the typical clinical stroke population.

When a patient has died or if a formal palliative end of life care process has been started at the point when the patient is identified as eligible for the study, individual patient consent will not be possible and it is likely to be distressing for a personal consultee to be approached regarding the research use of routinely collected healthcare data. The 90 day health outcome will not be relevant. Under these circumstances the local PI will sign an Early Mortality / Palliative Care Declaration Form to confirm that the patient has died or is in a formal palliative phase, and take responsibility for the use of routinely collected healthcare data for this research project.

Acute stroke has many effects upon neurological function and consciousness which can fluctuate for several days or even weeks. There may be unusual instances where a patient who has been entered into the study using this Early Mortality/Palliative Care Declaration form subsequently shows enough signs of improvement that supportive care is re-instated, and may still be alive at day 90. However, these are likely to be challenging clinical situations where seeking an alternative method of consent will be difficult because of the severe degree of remaining neurological impairment and time elapsed since admission. In these unusual scenarios, an alternative method of consent will not be pursued and the day 90 study specific assessment will not be conducted. Routinely available data collected as part of standard clinical care will be retained as per the original PI declaration and used in the analysis.

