#### ***Consent for patients who are only identified as study eligible after discharge from hospital***

Patients who have only been identified as study eligible after hospital discharge will receive an invitation letter, patient information sheet, consent form and pre-paid return envelope by post. Patients willing to take part in the study will be asked to return a completed consent form. Invited patients who have not returned a consent form within four weeks will receive one phone call from the local hospital research team. Thereafter, patients will only be further contacted about the study if a consent form is returned,

Figure 3 summarises the decision process for obtaining study consent,

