In instances where a participant/personal consultee cannot be contacted by telephone after one week of attempting to locate him/her, a postal questionnaire will be used. A postal questionnaire will also be used where telephone interview is not be possible (e.g. participant does not have a telephone). A single postal questionnaire with enclosed reply-paid envelope will be mailed. It will also be possible to collect 90 day study specific data by face to face interview conducted by NHS research support staff. This option will be used at the discretion of staff but predominantly when participants are currently hospital inpatients.

Where it has not been possible to obtain the 90 day study specific data by 6 months after stroke, NHS research support staff will use the routine hospital data administration systems to re-confirm whether the participant was alive or dead at 90 days. This is necessary because deaths in the community can take some time to appear in the routine hospital records. The mRS (primary outcome measure) is scored 6 for death[26].

All study data will be entered locally onto a secure online database maintained by Newcastle Clinical Trials Unit. Pseudo-anonymised participant identification codes will be used. Study paper CRF's will be kept securely in the local investigator site file.

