## 18. Statistical analysis

Analysis is by 'treatment allocated'; that is, primary and secondary efficacy and safety outcomes analyses will all use the study group allocation of the attending paramedic; only paramedics completing the study specific training will be considered as members of the intervention group. Thus, data will be analysed pragmatically according to paramedic group allocation, irrespective of the care process actually experienced by individual participants.

The primary end point measure is the proportion of participants who received intravenous thrombolysis. The primary analysis will compare the proportion of participants who received thrombolysis in the two arms of the study using logistic regression. Models will include various covariates and factors, including (but not limited to) participant age and gender and admission time and date (used to define a covariate to reflect background trends).

Secondary outcomes, including stroke severity 24 hours after thrombolysis (measured by an NIHSS score), inpatient mortality and dependency (modified Rankin Scale), will be analysed by appropriate ordinal and binary regression models, with appropriate adjustment for potential covariates and factors.

To address the second objective (that is, the impact of the intervention on various time intervals related to the emergency call), we will use appropriate statistical models. For time intervals between events which always happen (for instance, emergency call to hospital admission), we will employ linear models (after appropriate transformation), again adjusting for statistically significant covariates and factors; if the distributions of residuals are markedly non-normal, further transformation or bootstrapping will be considered. Residual diagnostics will also be used to identify outliers; identified outliers will be excluded and the analysis recalculated. For events which may or may not happen (for instance, emergency call to thrombolysis), we will analyse outcomes via binary regression models and survival analysis, comparing intervention and control arms using the framework of accelerated life testing; both approaches will again accommodate statistically significant covariates and factors.

Other clinical objectives will be addressed by appropriate descriptive statistical measures.

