### *Reporting*

Outcome descriptions, summaries and comparisons will be expressed in accordance with appropriate CONSORT guidelines[28], including estimates with 95% confidence intervals to summarise two-tailed tests at the 5% significance level.

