## **Sample size**

Sample size considerations are based on postulated and standardised statistical effects of the intervention on binary outcomes. A change from 0.1 to 0.13 (for instance, in the proportion of cases with a good mRS score at day 90) is equivalent to an effect of 0.1, while a change from 0.43 to 0.53 (for instance, in the proportion of patients receiving thrombolysis) is equivalent to an effect of 0.2.

In the initial protocol for this trial, sample size considerations assumed equal patient numbers per arm, allowed for 3% attrition for a primary outcome collected at day 90, used conventional values of 80% power and 5% significance, and a relatively small change between arms from 0.1 to 0.13 in the proportion of cases with a good mRS score at day 90, equivalent to a standardised statistical effect of 0.1. These considerations led to an initial recruitment target of 3640 (1820 cases per arm).

However, in early 2017, informal review of internal phase data showed that some key assumptions were unlikely to be met in practice. Specifically, overall recruitment was lower than anticipated, while intervention paramedic training completion rates meant a persistent imbalance in patient numbers in the two arms, with typically 8-10 control cases for every 5 intervention cases.

Following discussions with stakeholders (including both trial oversight committees and funders), it was agreed to amend the primary outcome to the proportion of patients receiving intravenous thrombolysis; postulating a change from 0.43 to 0.53 in the proportion of patients receiving thrombolysis, equivalent to a standardised statistical effect of 0.2. Sample size considerations were therefore re-assessed, factoring in attrition of 1%, power of 90% (and 5% significance), and an average cluster (patients per paramedic) of 5 with an intra-cluster correlation coefficient of 0.02. In addition, an imbalance of 2 control cases per intervention cases was incorporated. This gave a revised recruitment target of 1297 study participants (865 control cases versus 432 intervention cases).

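### 90-day mRS is completed from records for the dead but not for the living, and the missing-data rule reserves imputation for data that look MCAR, so a known-mRS analysis over-represents deaths

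*Protocol*

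**What the plan says.** **Day 90.** Protocol section 13 obtains the 90-day mRS by telephone, face-to-face interview or a single postal questionnaire. If that has failed by six months after stroke, staff are to "use the routine hospital data administration systems to re-confirm whether the participant was alive or dead at 90 days", and death counts as mRS 6.

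**Survivors not assessed.** Section 12 (iii) allows only routine data at 90 days for participants entered by an independent clinician. Section 12 (iv) gives no day-90 study assessment to a patient who entered by the early mortality or palliative declaration and then survived.

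**Entry.** For a patient already dead or in formal palliative care when identified, section 12 (iv) provides: "Under these circumstances the local PI will sign an Early Mortality / Palliative Care Declaration Form to confirm that the patient has died". The same form serves for palliative cases. Everyone else enters by own consent, a personal consultee or an independent clinician. Patients found only after discharge are invited by post, with one reminder call: "Thereafter, patients will only be further contacted about the study if a consent form is returned".

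**Analysis.** Section 18 says that "inpatient mortality and dependency (modified Rankin Scale), will be analysed by appropriate ordinal and binary regression models". Its Missing Data paragraph will consider imputation if nothing suggests a departure from MCAR; otherwise the Trial Statistician and Chief Investigator discuss the patterns. Section 20 maps pre-stroke and 90-day mRS to utilities for QALYs.

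**The concern.** Whether the 90-day mRS is known depends on its value. The top category, death, can be filled in for every enrolled participant; the categories 0-5 need contact. A model fitted to participants with a known mRS therefore sees too many sixes. The survivors missing by design are also unlikely to be typical: they lacked capacity and had no personal consultee, or had been judged palliative. The upper living grades may thus be thinned while grade 6 is kept whole.

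The Missing Data paragraph points the wrong way here. It makes imputation available where data look MCAR, the case in which a complete-case analysis is already unbiased, and leaves only a discussion where they do not. Missingness that can occur only in the living is not MCAR.

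At stake are the 90-day dependency comparison and, so far as observed 90-day mRS is used there, the QALYs. Section 20 also describes a model-based simulation of 90-day outcomes, so that share is not fully clear. The primary outcome, receipt of thrombolysis, is unaffected.

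**Working it through.** **The plan's own figures.** The protocol gives no figure for this enrichment. Its recruitment target concerns thrombolysis and reproduces: 783 control × 1.08 = 846, plus 423 intervention, gives 1268 analysable; divided by 0.99 this is 1281, 1.2% below the stated 1297. It says nothing about 90-day mRS.

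**Inputs from the protocol.** Inpatient mortality 17% (section 17, Expected adverse events), used as a stand-in for the 90-day death share d, for which no figure is given. Day-90 attrition 3% (Sample size, describing the initial protocol). Early mortality about 10% (section 12 (iv)), used as a stand-in for the share entering by declaration.

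**Assumed, because not stated.** Survivor ascertainment at day 90, r = 0.9, 0.8, 0.7. Enrolment of patients not entered by declaration, c = 0.9, 0.7, 0.5.

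**Who has a 90-day mRS**

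| Participant | If dead by day 90 | If alive at day 90 |
|---|---|---|
| Participant or personal consultee responds | 6 | 0-5 observed |
| Cannot be reached | 6, from records | alive, no mRS |
| Entered by independent clinician | 6, from records | alive, not contacted |
| Entered by palliative declaration | 6, from records | alive, not assessed |

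**Death share among known mRS.**
- 3% attrition, all in survivors: 0.17 / 0.97 = 17.5%.
- Otherwise d / [d + (1 − d)r]. For r = 0.9: 0.17 / 0.917 = 18.5%. For r = 0.8: 0.17 / 0.834 = 20.4%. For r = 0.7: 0.17 / 0.751 = 22.6%.

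**Effect on the arm comparison of mRS.** Among known mRS, the odds of grade 6 are d / [(1 − d)r].
- With equal r in both arms, r cancels at the cut between 5 and 6.
- It does not cancel at lower cuts. If g is the share of survivors with a good grade, the odds of a good grade are (1 − d)rg / [d + (1 − d)r(1 − g)]. With equal r and no true effect the odds ratio stays 1; with a true effect on d or g, it depends on r.
- With r = 0.85 against 0.75 and no true effect, the odds ratio for grade 6 among known mRS is 0.75 / 0.85 = 0.88. The split and its direction are illustrative.

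**Entry, a separate route.** If 10% enter by declaration and the remaining 90%, including the other 7% who die, enter with probability c, observed inpatient mortality is (0.10 + 0.07c) / (0.10 + 0.90c).
- c = 0.9: 0.163 / 0.91 = 17.9%.
- c = 0.7: 0.149 / 0.73 = 20.4%.
- c = 0.5: 0.135 / 0.55 = 24.5%.
- Equal true mortality and equal c in both arms give no spurious difference. With c = 0.75 against 0.65, the odds are 0.1525 / 0.6225 = 0.245 and 0.1455 / 0.5395 = 0.270, an odds ratio of 0.91. This split too is illustrative.

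**The case against.** **This is analysis-plan detail.** Imputation models are commonly left to the SAP, which is not shown, and nowhere does the protocol say that living non-responders are dropped. That is fair as to the predictors and the model. It does not cover the MCAR condition, which the protocol itself states and which sits badly with the missingness its own procedures create.

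**The size may be trivial.** The only day-90 attrition figure in the document is 3%, which moves 17.0% to 17.5%. This stands as the low end. That figure comes from the initial protocol and is not broken down by consent route, so it does not bound the effect.

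**Early deaths are included on purpose.** Section 12 (iv) argues that excluding them would make the sample less relevant to the clinical population. That is a sound reason and is not disputed; it bears on how absolute mortality is labelled.

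**Stronger readings.** A reader might infer three things that the text does not support.
- That survivors count only if they consent and respond. About a third of eligible patients are expected to be unable to consent, and section 12 (iii) lets them enter through a personal consultee or independent clinician.
- That day-90 non-response inflates mortality. The records establish alive as well as dead, so an enrolled non-responder still counts for mortality; only the mRS is affected.
- That the arm comparison of mortality is biased. This needs enrolment to differ by arm. The trial is unblinded (section 14), so a difference is possible, but identification is systematic from records and the consent routes are common to both arms. Nothing shows that a difference is likely.

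**Conclusion.** The point holds for the 90-day mRS. Its completion depends on vital status, some survivors are unmeasured by design, and the stated imputation condition is not met. Among participants with a known mRS, a 17% death share would appear as 17.5% under 3% attrition confined to survivors, and as 18.5% to 22.6% under assumed survivor ascertainment of 90% to 70%. These figures rest on inpatient mortality standing in for 90-day mortality and on response rates that the protocol does not give.

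For inpatient mortality the conclusion is narrower: the entry rule raises the absolute rate among participants whenever fewer than all the other eligible patients are enrolled, and bias between arms is conditional on unequal enrolment. Because only secondary and economic outcomes are touched and the remedy uses data already collected, this is a cheap improvement.

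**What to change.** 1. In section 18, including its Missing Data paragraph, state that participants confirmed alive at 90 days without a 90-day mRS stay in the mRS analysis, multiply imputed within grades 0-5 under MAR from discharge mRS, admission NIHSS, age, consent route and arm. Remove the MCAR condition for this outcome.
2. No survivor in the independent-clinician or palliative routes has an interview mRS, so separate effects for those routes cannot be estimated. Group them with the personal-consultee route, and say that their values are borrowed from participants of similar severity.
3. Report enrolled and eligible counts by consent route, and by arm where the eligibility log allows. Section 12 describes a site-specific log but does not say that it records arm.
4. Label absolute inpatient mortality as coming from a sample in which patients dead or palliative when identified entered without consent.
5. Treat any enrolment-weighted mortality analysis as a sensitivity analysis only. Consent route depends on capacity and early discharge, both likely to be prognostic, so weighting by arm and hospital need not remove the selection.

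The cost is modest extra analysis and slightly wider intervals. Discharge mRS, NIHSS, age and alive status are already collected, and no new patient contact is needed.

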## **14. Blinding**

In this trial, no specific blinding measures will be in place. Paramedics will know the study group allocation due to the nature of the intervention. Participants will be informed about group allocation if they ask for this information. NHS research support staff who will conduct the 90 day research assessment may be unaware of treatment group allocation but this will vary according to their involvement with participants on admission to hospital.

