## 12. Participant identification, recruitment and consent

Patients will be identified, recruited and consented to take part in this study after arrival at hospital and when the thrombolysis treatment assessment has been completed. There will be no study enrolment process in the pre-hospital setting. The purpose of the study is to demonstrate that the PASTA pathway can expedite the clinical delivery of a treatment which is already known to be effective in reducing future disability, but must be administered rapidly (thrombolysis). A formal research consent process performed by study paramedics or the admitting hospital team would delay hospital admission, brain imaging and / or thrombolysis treatment. Due to the time-dependent effect of thrombolysis, even a short delay could reduce the impact of the PASTA pathway. As the pathway does not involve a new treatment or technology but is attempting to expedite an existing hospital care process using a structured clinical assessment performed by paramedics, the risk of harm to intervention patients is low. Patients will still only receive thrombolysis treatment following review by a stroke specialist. Although they will not provide study information to patients, as per usual clinical practice, paramedics will explain to patients about possible care processes which may occur in hospital.

In order to identify study eligible patients, hospital research support staff will systematically review the ambulance and hospital records of all admitted patients with a confirmed hospital specialist diagnosis of stroke. From the records and using the identification numbers of paramedics involved in the study, staff will identify those patients who travelled with a study paramedic, aged over 18 years and were assessed by the paramedic within 4 hours of the stroke onset time (onset time as determined by the hospital stroke team). Patients meeting these enrolment criteria will subsequently be approached about taking part in the study.

Ideally, approach of patients will take place during their inpatient stay such that a timely discussion about the study can be held. However, some patients are discharged very early after admissions and should identification of an eligible patient occur after discharge from hospital, a postal invitation to take part in the study will be used.

A site-specific participant eligibility log will be maintained. The participant eligibility assessment process is shown in figure 2.

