**Day 90 (+/- 7 days) data:**

At day 90, both data related to hospital discharge from this continuous inpatient episode and health at 90 days after stroke will be collected.

*Data related to discharge due to completion of all inpatient care:*

Died during this inpatient episode for stroke (yes/no)  
Cause of death  
Date of death (if relevant)  
Discharge date or record that the patient is still an inpatient at day 90 (yes/no)  
If still an inpatient at day 90, has there been stroke recurrence  
Discharge destination at completion of this inpatient episode (own home, different private address (eg relative) care home, other)  
If discharged to a care home, was the patient previously resident / not previously resident  
Rehabilitation arranged at discharge (none, early supported discharge team, community rehabilitation team, both)  
Assistance with activities of daily living required at discharge (yes/no; if yes: what support received: informal carers/paid carers/both)  
If paid carers then how many visits per week provided at discharge  
Dependency at discharge (mRS)

*Data related to day 90 health:*

Died after stroke event discharge but prior to 90 days (yes/no)  
Date of death (if relevant)  
Cause of death (if available)  
Readmission(s) to hospital since discharge; reason for admission(s), length of stay(s).  
Readmission was due to stroke recurrence (yes, no)  
Current (90 day) residence (hospital, home, different private address, care home, other).  
Current (90 day) dependency (simplified questionnaire mRS[25])  
Community rehabilitation since discharge (therapy received (yes/no); received at home/hospital/both; number of weeks received; less than, equal to or great than one appointment/week).  
Current (90 day) assistance with activities of daily living (yes / no; if yes: what support received: informal carers/paid carers (how many visits per week) /both)

For all participants, confirmation that stroke remains the diagnosis assigned for the event where consent was obtained. If not, the new diagnosis assigned.

Day 90 data consists of both routinely collected clinical data and study specific data. Routinely collected clinical data will be transcribed from routine medical records onto a study specific CRF. Study specific data will be collected by face to face interview, telephone interview or by postal questionnaire. Telephone interview with the participant or consultee will be the main method, undertaken by NHS research support staff.

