## **15. Staff training and awareness**

For paramedics based within stations / teams randomised to deliver the PASTA pathway, study specific training will be provided via a securely hosted online video. This will include explanation of the study objectives, demonstration of the PASTA pathway processes, completion of trial documentation and responses to adverse events. After watching the video, paramedics will complete an online MCQ knowledge assessment. Paramedics who do not provide correct responses to all questions will be invited to watch the online video again and repeat the MCQ. Paramedics who correctly answer all questions will be identified as trained and issued with study documentation. If paramedics based with stations / teams allocated to delivering the intervention do not wish to assist with the study, they will be able to opt out of training.

Paramedics based with stations / teams randomised to continuing standard stroke care will be informed that there is an ongoing study of pre-hospital assessment for stroke patients, but not be given any further information about the study and asked not to change their practice. Paramedics allocated to continuing standard stroke care will also be able to opt out of the study if they wish.

To determine whether the characteristics of paramedics participating in each study group differ, the following will be obtained about individual randomised paramedics during the course of the study: age, gender, highest qualification, years qualified as a paramedic, years in service at employing ambulance service, NHS job band, job title. These characteristics will be obtained from ambulance service records if possible and if not, direct from paramedics by means of an electronic survey.

NHS research support staff based in hospitals taking part in the study will receive study specific training. This will cover identification, recruitment and consent of participants, data collection and the 90 day research assessment, and other study processes such as use of the online database.

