### **1. Medically stable patients within the North East region who were attended by an intervention paramedic and provided their own consent to participate in the pilot or main trial.**

Participants with a range of stroke severities and treatment experiences will be recruited. Individual face to face interviews will be conducted. Whenever possible, interviews will be arranged within 7 days of admission to facilitate recall of experiences and details. Interviews will last up to 30 minutes. Participants enrolled in both the internal pilot trial (up to 12) and main trial (up to 40) will be included. The number of North East hospital sites where patients will be identified for invitation will be determined during the trial according to parameters such as recruitment rate and different stroke service design.

At agreed time intervals during the trial recruitment period the researcher conducting the interviews will make contact with a member of the research support staff at a chosen North East hospital site. Without receiving identifiable information, the researcher will enquire about the demographics (e.g. age, sex, stroke severity, thrombolysis received) of the participants who are allocated to the intervention group, received the PASTA pathway and who gave their own consent to take part in the trial in the previous seven days. Using the demographics, the researcher will select the participants to be invited for interview. A member of the research support staff will subsequently approach the nominated participants to discuss the interview process and provide an information sheet. After allowing sufficient time for participants to decide whether to take part in the interview and an opportunity to ask questions, the member of the research support staff will obtain consent to provide their contact details to the researcher conducting the interview.

The researcher conducting the interview will arrange a mutually convenient time to visit the patient (either in hospital or in their own home if recently discharged) to conduct the interview. Consent to be interviewed will be obtained immediately prior to the start of the interview (in writing).

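### Day-90 assessors' knowledge of trial arm is neither controlled nor recorded, which leaves the 90-day mRS and the outcomes built on it open to a bias of unknown size

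*Protocol*

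**What the plan says.** Section 14 (Blinding) opens: "In this trial, no specific blinding measures will be in place". On participants it adds: "Participants will be informed about group allocation if they ask for this information". Of the staff who do the 90-day assessment it says that they "may be unaware of treatment group allocation but this will vary according to their involvement with participants on admission to hospital".

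Section 13 names who collects the day-90 data: "Telephone interview with the participant or consultee will be the main method, undertaken by NHS research support staff". A postal questionnaire is the fallback, and face-to-face interview is possible. Dependency is taken with a simplified mRS questionnaire, and death scores 6.

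Other sections show what else this staff group does:

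- Section 12: participants are found from ambulance and hospital records, "using the identification numbers of paramedics involved in the study".
- Section 13: ambulance data are transcribed to a CRF on which one item (rapid response paramedic) applies to the intervention group only. A separate paramedic CRF exists only for participants brought in by a trained intervention paramedic. Study data are entered locally.
- Section 15, on the training of these staff: "This will cover identification, recruitment and consent of participants, data collection and the 90 day research assessment".
- Section 21, group 1 (North East): site staff describe intervention participants to the interviewer, and then "A member of the research support staff will subsequently approach the nominated participants to discuss the interview process and provide an information sheet". For group 2 (elsewhere) they post the invitations, and the researcher selects from a database that holds the study group.

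**The concern.** The mRS rests partly on judgement, so an assessor who knows the arm can score it differently without intending to. Paramedics and admitting teams cannot be blinded here. The day-90 contact is another matter: it comes three months later and is mostly by telephone. Section 14 nevertheless leaves the assessor's awareness to chance. It does not ask for a different person at day 90, does not ask participants to withhold their arm, and does not ask the assessor to note what they know.

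At stake are secondary and economic results: 90-day mRS and assistance at 90 days (sections 4 and 6.2), and QALYs estimated from pre-stroke and 90-day mRS (section 20). These are the results that would show whether the pathway changed patients' health rather than only their treatment. As written, the final report could not say how often assessors knew the arm. This is a matter of trial conduct that belongs in the protocol, so an unseen SAP would not settle it.

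**Working it through.** **Does any step limit or record awareness?** Sections 12 to 15 and 21 were set side by side.

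| Step | Who | What it can reveal |
|---|---|---|
| Match patient to study paramedic (12) | Site research staff | Paramedic identity; section 12 does not say that the list shows the arm |
| Transcribe ambulance data; intervention-only item and paramedic CRF (13) | Site research or trained clinical staff | Arm |
| Enter the local database (13), which holds the group (21) | Site staff | Possibly arm; what the screen shows is not stated |
| Interview invitations (21) | Site research staff | Arm, for a purposive sample |
| Day-90 telephone mRS (13) | Site research staff | No separation from the rows above is required |

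No section states a step that limits or records the assessor's knowledge.

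**The plan's own figures.** Section 18 gives 0.43 against 0.53, 90% power, 5% two-sided, 2:1 allocation, 5 patients per paramedic, ICC 0.02 and 1% attrition. The design effect is 1 + (5 - 1) × 0.02 = 1.08. Standard two-proportion formulae give totals from 1281 (no continuity correction) to 1330 (with it), against the stated 1297. Power at 856/428 is 90.4%. The sample size reproduces and is not in question.

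**Hypothetical effect of a scoring shift.**

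- Inputs from section 18: 856 control and 428 intervention analysable, design effect 1.08, and a good day-90 mRS proportion of 0.10 (the only such rate in the document, from the superseded calculation).
- Assumptions: no true effect; all 1284 analysable at day 90; a second base rate of 0.35; and a net shift *d* in the observed proportion across the whole intervention arm.

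Effective sizes: 856/1.08 = 792.6 and 428/1.08 = 396.3.

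With *q* = *p* + *d*, SE = √[*p*(1 - *p*)/792.6 + *q*(1 - *q*)/396.3], and the rejection probability is Φ(*d*/SE - 1.96) + Φ(-*d*/SE - 1.96).

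For *p* = 0.10 and *d* = 0.02: SE = √(0.09/792.6 + 0.1056/396.3) = 0.0195; *d*/SE = 1.026; rejection probability = 0.177. Using *p* for both arms' variance instead, SE = 0.0185 and the result is 0.192. The ranges below reflect these two variance choices.

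| Net shift | Base 0.10 | Base 0.35 (assumed) |
|---|---|---|
| 1 point (a 2-point shift in half the arm) | 8% | 6% |
| 1.5 points (a 3-point shift in half the arm) | 12-13% | 8% |
| 2 points | 18-19% | 10% |
| 3 points | 32-37% | 17-18% |

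**The case against.** Section 14 discloses that awareness will vary, so this is a stated limitation of a pragmatic trial run by site staff, not a contradiction. That is fair, but disclosure neither reduces nor measures the problem.

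A reader might infer that most assessors will know the arm. The document does not support this. It gives no proportion, and section 14 says that some assessors may be unaware. Both arms have study paramedics, and section 12 does not say that the identification list shows allocation. A form kept at the hospital need not have been read by the day-90 caller. The North East interviews are capped at 12 pilot plus 40 main-trial patients, and 52/432 is about 12% of the intervention target; the number elsewhere is not set. Exposure is uncontrolled, not universal.

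Existing features also limit scoring discretion: the simplified questionnaire, the postal form and the fixed score for death. Participants entered on an independent clinician's declaration are not contacted at day 90, and those entered on the early mortality or palliative care form have no study-specific assessment (section 12). So some participants have no interviewer-scored mRS, and the whole-arm shifts in the table sit towards the upper end. Using 856/428 is also generous, since it rests on 1% attrition for thrombolysis, whereas the superseded day-90 outcome allowed 3%. The table tests a dichotomised mRS, while section 18 plans ordinal and binary models. All of this stands and reduces the likely size. None of it limits or measures knowledge of arm.

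**Conclusion.** The point holds as one about secondary and economic outcomes. The day-90 assessor's knowledge of arm is left uncontrolled and unrecorded, although the assessor comes from a group whose other tasks can reveal it.

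The primary outcome, receipt of thrombolysis, is not scored at day 90 and is unaffected. Section 13 still labels mRS the primary outcome measure, against sections 4, 6.2 and 18; the point here does not rely on that label.

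A reader might go further and conclude that the 90-day mRS result will be biased, or biased in favour of the pathway. The document gives no basis for either the size or the direction of a shift. The 2- and 3-point shifts are assumptions. What they show is that, with a standard error of about 1.9 points at a rate of 0.10, even a small net scoring shift would matter: about 18-19% false positives instead of 5% at base 0.10 and 10% at base 0.35 for 2 points across the whole arm, and about 8% and 6% if only half the arm is affected.

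**What to change.** Amend sections 13 and 14:

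1. Where a site has more than one trained staff member, the day-90 contact is made by one who did not screen, consent or invite that participant to interview.
2. The day-90 form does not display arm or paramedic number, and the participant (or the consultee answering) is asked at the start not to mention the arm.
3. Before the call, the assessor records whether the arm is known. The frequency is reported by arm, descriptively only.

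The treatment effect should not be split by this flag and read as a bias check. Awareness arises after randomisation, and intervention patients generate extra paperwork, so it is likely to differ by arm and with staff involvement at admission. A comparison within levels of the flag would be confounded.

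Cost: a small form and database change and a rota instruction to existing staff, with no extra patients and no change to the sample size. The downside is less flexibility over who makes the call. Sites with a single research nurse can do only items 2 and 3.
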